##### Comparison II: TCC arm vs control arm

The primary outcome in comparison 2 is the proportion of all timely routine ANC visits that a woman was eligible for, where the woman attended (Table 2). The first ANC booking visit is excluded, and each timely routine visit will be counted separately as a singular opportunity to succeed or fail in attendance.

##### Comparison III: QID + TCC arm vs control arm

The primary outcome in comparison 3 is the product of the quality of care (comparison 1) and the utilization of care (comparison 2) to assess the effective coverage. For example for anemia, it is the proportion of all timely routine ANC visits where anemia should have been screened for and/or managed, where the woman attended and anemia was appropriately screened for and/or managed.

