#### Primary outcomes

##### Comparison I: QID arm vs control arm

The primary outcome in comparison 1 is the proportion of women who receive appropriate screening and management of anemia, hypertension, and diabetes (Tables 3, 4, 5, 6, and 7). For example for anemia, the proportion is calculated by identifying the number of ANC visits where anemia should have been screened for and/or managed (denominator), and among them where anemia was appropriately screened for and/or managed (numerator). Only the first step in the management algorithm will be included (Tables 3, 4, 5, 6, and 7). Pregnant women with documented ongoing anemia, hypertension, or diabetes prior to the timely routine visit will not be included in the denominator for appropriate screening and management of anemia, hypertension, and diabetes respectively.

**Table 3 Tab3:** Anemia screening test, result, and appropriate management

Hemoglobin test at first visit, 24–28, and 36 weeks’ gestation		
Hb ≥ 11 g/dL	Hb 10.9–7 g/dL	Hb < 7g/dL
No further action	Hb after 1 month	Refer to hospital

**Table 4 Tab4:** Hypertension screening test, result, and appropriate management prior to 20 weeks’ gestation

Blood pressure prior to 20 weeks’ gestation, test at the first visit and at 16, 18–22 weeks’ gestation	
SBP < 140 mmHg and DBP < 90 mmHg	SBP ≥ 140 mmHg, DBP ≥ 90 mmHg
No further action	Refer to high-risk clinic

*SBP* systolic blood pressure, *DBP* diastolic blood pressure

**Table 5 Tab5:** Hypertension screening test, result, and appropriate management at or after 20 weeks’ gestation

Blood pressure at or after 20 weeks’ gestation, test at 18–22, 24–28, and 36 weeks’ gestation		
SBP < 140 mmHg and DBP < 90 mmHg	DBP 90–99 mmHg, SBP 140–149 mmHg	DBP ≥ 100 mmHg, SBP ≥ 150 mmHg
No further action	New BP within 4 days	Refer to hospital

*SBP* systolic blood pressure, *DBP* diastolic blood pressure

**Table 6 Tab6:** Diabetes screening test, result, and appropriate management prior to 24 weeks’ gestation

Urine glucose test at booking prior to 24 weeks’ gestation	
Negative	Positive
No further action	Blood glucose test

**Table 7 Tab7:** Diabetes screening test, result, and appropriate management at or after 24 weeks’ gestation

Blood glucose test at 24–28 weeks’ gestation		
RBG < 105 mg/dL, FBG < 95 mg/dL	RBG 105–140 mg/dL, FBG 95–126 mg/dL	RBG ≥ 140 mg/dL, FBG ≥ 126 mg/dL
No further action	New blood test within 3 weeks	Refer to a diabetes clinic

*RBG* random blood glucose, *FBG* fasting blood glucose

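### Comparison III's primary outcome is stated as a product of two rates that use different visits, so it need not equal the joint visit-level proportion given as its example

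*Protocol article*

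**What the plan says.** All places are in the protocol article.

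- **Comparison III, definition.** "The primary outcome in comparison 3 is the product of the quality of care (comparison 1) and the utilization of care (comparison 2". The stated purpose is to assess effective coverage.
- **Comparison III, anemia example.** The base is "the proportion of all timely routine ANC visits where anemia should have been screened for and/or managed", and success is a visit "where the woman attended and anemia was appropriately screened for and/or managed".
- **Comparison I.** The headline outcome is "the proportion of women who receive appropriate screening and management of anemia, hypertension, and diabetes", but the worked example counts visits, starting by "identifying the number of ANC visits where anemia should have been screened for and/or managed (denominator". It does not say whether visits that were due but not attended belong in that denominator. Table 3 sets the anemia schedule: "Hemoglobin test at first visit, 24–28, and 36 weeks’ gestation". Women with a documented ongoing condition are removed from that condition's denominator.
- **Comparison II.** The outcome is attendance over all the timely routine visits a woman was eligible for, whatever condition is tested there. "The first ANC booking visit is excluded". Table 2 lists five routine windows and shows the first visit separately. No removal of women with a known condition is stated.
- **Statistical methods.** The primary analysis uses individual-level data and takes clustering into account.

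**The concern.** The definition refers by number to two outcomes with different visit sets, and then gives an example that uses a third. A product of rates equals a joint proportion only when quality is conditional on attendance and both factors run over the same visits.

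Taken literally, the product brings two things into effective coverage that the example leaves out. One is the quality of care at booking, a visit to which attendance does not apply. The other is attendance at routine visits where the condition is not tested. How much this matters varies by condition. In Table 2, hemoglobin is due at two of the five routine windows, blood glucose at one, and blood pressure at all five.

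At stake is the estimate for the only primary outcome of the combined arm. If the interventions act mainly on routine visits, booking quality dilutes the effect measured by the product.

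**Working it through.** **No figure to reproduce for this outcome.** The Sample size section gives no control rate or power for Comparison III. Its general statement (30% against 45%, 80% power) does reproduce. The design effect is 1 + ((1.69² + 1) × 172 − 1) × 0.05 = 34.11. With 34 clusters per arm the effective size is 34 × 172 / 34.11 = 171.4, giving power of 82% (79% with continuity correction). That does not bear on the definition.

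**When the two forms agree.** P(attended and correct) = P(attended) × P(correct | attended). If both factors cover the same visits, the ratio of product to joint proportion is exactly 1.00.

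**Visit sets for anemia, as written**

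| | First visit | Routine visits counted | Known anemia removed |
|---|---|---|---|
| Comparison I | yes | 24–28, 36 weeks | yes |
| Comparison II | no | all five | not stated |
| Comparison III example | no | 24–28, 36 weeks | not stated |

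**Inputs for the illustration.** The article gives control ranges of 30–85% for Comparison I and 34–53% for Comparison II, and uses 30% for anemia at 24–28 weeks. The rest is assumed:

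- Attendance at the five windows is 53, 50, 45, 40 and 34%.
- Correct hemoglobin care among attended visits is 85% at booking, 30% at 24–28 weeks and 40% at 36 weeks.
- Every woman attends booking and is eligible for all five routine visits.

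**Control level**

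- Quality including booking: (0.85 + 0.45 × 0.30 + 0.34 × 0.40) / (1 + 0.45 + 0.34) = 1.121 / 1.79 = 0.626
- Pooled attendance: (0.53 + 0.50 + 0.45 + 0.40 + 0.34) / 5 = 0.444
- Product: 0.626 × 0.444 = 27.8%
- Joint: (0.45 × 0.30 + 0.34 × 0.40) / 2 = (0.135 + 0.136) / 2 = 13.6%

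**Treatment effect.** Assume routine attendance rises by 20% (relative), routine quality rises by 50% and booking quality is unchanged.

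- Quality: (0.85 + 0.54 × 0.45 + 0.408 × 0.60) / (1 + 0.54 + 0.408) = 1.3378 / 1.948 = 0.687
- Pooled attendance: 0.444 × 1.2 = 0.533
- Product: 36.6%, a ratio to control of 36.6 / 27.8 = 1.32
- Joint: (0.243 + 0.2448) / 2 = 24.4%, a ratio to control of 1.80

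If instead quality rises by 10% at every visit including booking, with the same attendance gain, the ratios are 1.27 and 1.32. The effect estimates separate mainly when booking and routine visits respond differently.

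**Range of product divided by joint** (30–85% and 34–53% assigned freely to visits, which is an assumption)

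- Both mismatches together: 0.54 to 2.79. The low end is 0.2425 / 0.4505 and the high end 0.2848 / 0.102.
- First visit alone: 0.61 to 2.09.
- Pooling attendance over five windows alone: 0.416 / 0.53 = 0.79 to 0.454 / 0.34 = 1.34.
- Equal quality at all anemia visits and equal attendance at all routine visits: 1.00.
- Quality taken over all due visits, attended or not, on one visit set: the joint proportion is then the quality rate itself, and the ratio equals attendance, 0.34 to 0.53.

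**The case against.** The strongest reply is that the article has only one definition. The example follows directly on the word product and can be read as saying what it means. It fixes the denominator, the numerator and the visit as the unit. Its restriction to routine visits already leaves booking out, because Table 2 separates the two. Exact visit coding is also commonly left to a fuller document than a journal article.

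Much of this stands. A reader might infer that a product and a joint proportion are inherently different quantities; the chain rule shows they are not. A reader might also infer a contradiction with the individual-level analysis, since a product of two aggregate rates has no visit-level value. The example does have one, so the Statistical methods section supports the joint reading rather than exposing a conflict. Finally, a reader might fear that the definition could be chosen by result. The Blinding section has independent monitors hold the allocation codes until the analyses are complete, which limits that risk, though it does not settle which definition is primary.

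The reply does not remove the explicit cross-reference. The text names the outcomes of Comparisons I and II as the factors, and those outcomes, as the article itself defines them, do not share a visit set. That is a stated rule at odds with its own illustration, not detail left for later.

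**Conclusion.** Wrong as written, of moderate severity. The literal product of the Comparison I and Comparison II outcomes is not in general the quantity in the Comparison III example, and using it could change both the level and the treatment effect of the combined arm's only primary outcome.

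The documents do not establish that the two forms will differ greatly. The 28% against 14%, and the effect ratios of 1.32 against 1.80, rest on assumed visit-specific rates and assumed gains. Over the stated control ranges the product could be about half the joint proportion, equal to it, or nearly three times it, so even the direction is open. Less favorable inputs shrink the gap: with 60% quality at booking, 50% at both later visits and the same attendance, it is 24.7% against 19.8%.

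Whether Comparison I's denominator means attended or due visits is also not fixed. An 85% control rate could not arise over due routine visits attended at most 53% of the time. This favors the attended-visit reading but does not prove it, since the 85% may come from booking.

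**What to change.** Replace the product wording with the indicator that the example already describes. For each condition, take every eligible timely routine visit at which that condition is due, exclude booking, and apply Comparison I's exclusion of women with a known condition. Count success if the woman attended within the window and the condition was appropriately screened for and managed; otherwise count failure. Analyze this in the planned individual-level model with clustering.

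Report two components over the same visits: attendance, and quality given attendance. Their product then equals the primary outcome by construction, which keeps the effective-coverage interpretation. Comparisons I and II can keep their own visit sets as separate primary outcomes, but Comparison I should state whether its denominator is attended or due visits.

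Cost: one paragraph and analysis code; no new data.

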##### Effect on healthcare equity

We will assess the effects of the interventions on the primary outcomes across equity measures used in routine statistics in Palestine. The data points include average monthly household incomes (less than 200; 200–900; 901–1824; 1825–3054; and > 3055 Israeli new Shekel), mother’s years of education (< 10; 10–13 years; > 13 years), age at marriage (less than 20; 21–25; 26–30; 31–35; 36–40; greater than 40 years), and age at first pregnancy (less than 20; 20–25; 26–30; 31–35; 36–40; greater than 40 years).

##### Other outcomes

We will assess the proportion of women receiving appropriate screening and appropriate management separately at each visit for anemia, hypertension, and diabetes. We will also measure the retention rate from ANC to PPC and timely screening and management of fetal growth. The data entry in the eRegistry is continuous and the randomization permanent, which enable the analysis of overall health outcomes in a continuous and longitudinal manner for each individual woman. We might assess other outcomes if the intervention(s) shows an effect.

### Timeline

Care providers in PHCs randomized to the TCC intervention have had the opportunity to register pregnant women to the text message service since June 2019. Care providers in PHC randomized to the QID intervention received access to the QID December 2019. We expect to reach the target sample size after approximately 6 months (Fig. 4).

**Fig. 4 Fig4:**
[figure not shown]
Schedule of enrolment, interventions, and assessments (SPIRIT figure)

### Sample size

Sample size calculations for the primary outcomes were performed in STATA “clustersampsi” (StataCorp. 2015. Stata Statistical Software: Release 14. College Station, TX: StataCorp LP). We estimated the minimum detectable difference for comparison of each intervention arm with the control arm without assuming the effect of multiple comparison (using a single control to each intervention arm). The control prevalence for the primary outcome, using data from the eRegQual CRCT, ranged from 30 to 85% for comparison I (QID vs control) and from 34 to 53% for comparison II (TCC vs control) (unpublished results). The 138 eligible clusters have an average of 172 new pregnancies per 6 months (ranging from 23 to 1500) and a 1.69 coefficient of variation of cluster size (2016 data). We assumed a priori intra-cluster correlation coefficient (ICC) of 0.05 and set the statistical significance level to 5%. We are 80% powered to detect an estimated relative 50% increase for the outcomes with the smallest control prevalence (e.g., improving anemia screening and management at 24–28 weeks’ gestation from 30 to 45%).

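### The claim of 80% power for a relative 50% increase does not extend to Comparison III outcomes with low control prevalence, where the plan's own inputs give about 30–46%

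*Protocol article*

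**What the plan says.** The Sample size section opens by saying that it concerns the primary outcomes, and sets its scope as follows: "We estimated the minimum detectable difference for comparison of each intervention arm with the control arm". The trial has three intervention arms: QID, TCC, and both together.

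For the control prevalence it reports that the values "ranged from 30 to 85% for comparison I (QID vs control) and from 34 to 53% for comparison II (TCC vs control"). No value is given for Comparison III. The power statement follows: "We are 80% powered to detect an estimated relative 50% increase for the outcomes with the smallest control prevalence". Its example is "improving anemia screening and management at 24–28 weeks’ gestation from 30 to 45" percent.

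The section on Comparison III defines that outcome: "The primary outcome in comparison 3 is the product of the quality of care (comparison 1) and the utilization of care (comparison 2"). Using anemia as its example, it counts a success only when the woman attended a timely routine visit at which anemia care was due and that care was appropriate.

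**The concern.** A product of two proportions is smaller than either of them. If the power statement covers all three arms, as the scope sentence implies, then 30% is not the smallest control prevalence among the primary outcomes. The anemia outcome chosen as the example belongs to a routine visit (Table 2), so it also enters Comparison III, multiplied there by an attendance rate of at most 53%.

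A given relative increase is a smaller absolute difference when the starting prevalence is lower, and is harder to detect. Effective coverage under the combined intervention is a primary objective. A reader who relies on the 80% figure could take a null result on a low-prevalence Comparison III outcome as stronger evidence against an effect than the design can provide.

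**Working it through.** **Inputs.** From Sample size: 138 clusters, mean cluster size m = 172 per 6 months, coefficient of variation 1.69, ICC 0.05, significance level 5%, no multiplicity adjustment. From Allocation: a 1:1:1:1 ratio, so 138/4 = 34.5 clusters per arm on average. Sidedness is not stated; two-sided is assumed.

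**Effective sample size**
- Design effect = 1 + ((CV² + 1) × m − 1) × ICC = 1 + ((2.856 + 1) × 172 − 1) × 0.05 = 34.11.
- Effective n per arm = 34.5 × 172 / 34.11 = 174.0.

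**Power formula** (two proportions, normal approximation, p̄ the mean of p1 and p2)

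Power = Φ[ (p2 − p1 − 1.96 × √(2p̄(1 − p̄)/n)) / √((p1(1 − p1) + p2(1 − p2))/n) ]

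**The plan's own example, 30% to 45%.** (0.150 − 1.96 × 0.0519) / 0.0513 = 0.94, so power is 82.7%. With a continuity correction it is 79.6%. The value detectable with 80% power is 44.5%, which rounds to the stated 45%. The stated example reproduces.

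**Implied Comparison III control prevalence for that outcome**
- With the lowest attendance: 0.30 × 0.34 = 10.2%.
- With the highest attendance: 0.30 × 0.53 = 15.9%.

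**A relative 50% rise from those values**
- 10.2% to 15.3%: (0.0510 − 1.96 × 0.0358) / 0.0357 = −0.54, power 29.6%.
- 15.9% to 23.85%: (0.0795 − 1.96 × 0.0428) / 0.0426 = −0.10, power 45.9%.

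With the continuity correction these become 24.3% and 40.6%.

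**Across the implied Comparison III range**

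| Control prevalence | Derivation | Power for +50% | Detectable with 80% power |
|---|---|---|---|
| 10.2% | 0.30 × 0.34 | 29.6% | 21.1% (+107%) |
| 15.9% | 0.30 × 0.53 | 45.9% | 28.3% (+78%) |
| 28.9% | 0.85 × 0.34 | 80.4% | 43.3% (+50%) |
| 45.1% | 0.85 × 0.53 | 99.0% | 60.0% (+33%) |

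Solving for the control prevalence at which a relative 50% rise has exactly 80% power gives 28.7%.

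**Sensitivity**
- *More visits or women per cluster.* As m grows, effective n per arm approaches 34.5 / (3.856 × 0.05) = 178.9. Power is then at most 30.3% from 10.2% and 47.0% from 15.9%.
- *Smaller ICC, from 10.2%.* Power is 60% at an ICC of 0.02 and 86% at 0.01.
- *Both components rise by 50%.* The ratio is 1.5² = 2.25. From 10.2% (to 22.95%) power is 89.6%; from 15.9% (to 35.8%) it is 99%.
- *Both components rise by 25%.* The ratio is 1.25² = 1.5625. From 10.2% (to 15.9%) power is 35.4%.

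**The case against.** Three objections have weight.

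First, the power sentence is correct for the figures printed beside it. The prevalences listed are for Comparisons I and II, the example sits at the bottom of the Comparison I range, and it reproduces. On this reading Comparison III was left out of the paragraph, and a fuller protocol may hold its figures. That would excuse the absence of detail. It does not settle the wording, because the section claims to cover each intervention arm and the power sentence carries no restriction.

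Second, a relative 50% rise may be a modest benchmark for an arm that receives both interventions. If each component rose by the 50% used elsewhere, power from 10.2% would be about 90%; 80% power there needs about 44% on each, since √2.066 = 1.437. This is a fair point about what the arm might achieve, but the plan does not state such an effect for Comparison III.

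Third, 10.2% is a corner value that pairs the lowest quality figure with the lowest attendance figure. The article does not say which attendance rate belongs to the 24–28 week visit, so only the range 10.2–15.9% can be supported. Power is below 50% throughout it.

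A reader might infer more: that Comparison III as a whole, and so a third of the primary objectives, lacks the stated power. The documents do not support that. Outcomes at 28.9% and 45.1% reach 80% and 99% power for the same relative rise.

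**Conclusion.** The point holds in limited form. As worded, the claim of 80% power for a relative 50% increase takes in Comparison III, but the plan's own inputs do not deliver it for Comparison III outcomes with control prevalence below about 28.7%. For the anemia outcome used as the example, power is about 30–46%, and the rise detectable with 80% power is 78–107% in relative terms.

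This rests on the stated ICC of 0.05 and coefficient of variation of 1.69, on a two-sided 5% test, and on multiplying the Comparison I and II control figures as the protocol's definition directs. The calculation for Comparisons I and II is not in question. The outcomes, the analysis and the allocation are unaffected; what needs correcting is the stated reach of the power claim.

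**What to change.** Limit the sentence on 80% power and a relative 50% increase to Comparisons I and II. Add a sentence for Comparison III with its implied control prevalence, about 10–45%, and its own differences detectable with 80% power: 10% to 21%, 16% to 28%, 29% to 43%, and 45% to 60%. State which attendance rate goes with each quality outcome, so that the range can be replaced by one value per outcome. If the investigators expect both components to improve in the combined arm, they should state that effect and the power it gives.

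The cost is a change of text and a less favourable stated figure for some Comparison III outcomes. No clusters or women are added.

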### Recruitment

PHCs that fulfilled the recruitment criteria were randomized to one of the four arms. Healthcare providers working in PHCs randomized to one or both of the interventions received training as described (the “Intervention” section).

No financial or non-financial incentives are or will be provided to the woman, public health officers, or healthcare providers at the PHCs included in the trial.

### Allocation

Statisticians at the Center for Intervention Science in Maternal and Child Health (CISMAC), University of Bergen, Norway, performed the randomization independently without any influence from the research team.

PHCs were allocated to the TCC intervention, QID intervention, TCC and QID intervention, or control group with an equally 1:1:1:1 randomization ratio. The randomization was stratified by the point in time the eRegistry was implemented, and constrained on laboratory availability, ultrasound availability, and the size of the PHC.

In total, 10,000 randomization allocations were generated. The 10% best and balanced allocations with the least differences between the arms for the given covariates were identified, and one of these allocations were randomly selected for the trial [36].

### Blinding

Healthcare providers and women attending care at PHCs included in the trial are blinded to the outcome measures. Women are expected to be blinded to the allocation of the QID intervention, but not to the TCC intervention due to the nature of the intervention. Healthcare providers are not blinded to the allocation of any intervention.

Data will be extracted from the eRegistry and transformed to anonymous datasets by blinded data analysts at PNIPH. Allocation codes will be generated for each primary outcome separately (e.g., A, B, C, and D; E, F, G, and H; I, J, K, L, and M). Our independent trial monitors (CISMAC) will keep the codes, which will be provided as allocation groups (intervention TCC, intervention QID, intervention TCC and QID vs control) for each set of outcomes after the completion of analyses.

